### Intervention(s)

Of the 20 participating clinicians, 10 will be randomized to weekly teleECHO sessions. It is both impractical and inconsistent with high ethical standards to prevent the remaining 10 clinicians from accessing the dissemination of best practices via monthly interactive webinars and quarterly short courses, as these will be made available to providers across the USA. The subsections below provide more details on the intervention and an overview of the flow of clinicians through the study can be found in Fig. 1.

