Survey constructs and question formats are drawn from a deep body of existing research evaluating the impact of ECHO models on clinicians’ outputs and outcomes [15]. Survey methods and constructs were also studied among all randomized controlled trials of clinician-level outcomes globally captured in the Health Care Provider Performance Review, a multi-year systematic literature review process of global health worker performance evaluations [24]. To measure knowledge and self-efficacy, providers will be asked to state their relative agreement with statements related to their care of PCC patients, measuring from “strongly agree” to “strongly disagree” [15]. This 5-point response format will be held constant across survey knowledge and self-efficacy statements, to allow for an index to be created for use in more exploratory analyses. Open-ended response fields will be provided to some questions to allow providers to document specific examples of practice changes. Lastly, constructs probing overall provider satisfaction and utility with content will be measured to inform the acceptability and feasibility of the intervention.

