
### Statistical analysis

Analyses will be based on the intention-to-treat principle. All patients will be analyzed in the condition to which the clinician to which they were assigned was randomized regardless of compliance or fidelity. A “per-protocol” secondary analysis will be considered if compliance or fidelity of clinicians is a concern. All tests of significance will be two-sided and a *p*-value of 0.05 will be considered statistically significant. Group comparisons will be conducted on all the measured baseline patient characteristics to identify potential systematic differences between patients in each study arm. Identified patient characteristics that are not balanced will be used as covariates in the subsequent modeling of the data. Potential differential attrition between the two study arms will be compared and adjusted for in analyses. Analyses of differences in outcomes at both the patient- and clinician-level will include a linear mixed model to compare change in outcomes from baseline to each post-baseline assessment between the randomized study arms. Fixed effects will include the study condition, assessment, study condition-by-assessment interaction, baseline measure, and any unbalanced covariates. Assessment will be treated as a categorical variable, and an unstructured variance–covariance structure will be used. Results will be reported as point estimates (mean differences between groups) and interval estimates (95% confidence intervals). An intervention effect will be concluded if the *p*-value for the study arm-by-assessment interaction contrast in the model at the final assessment is statistically significant. This approach uses all available data and is robust to data missing at random (MAR).

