Changes over time among clinicians in the intervention condition will be analyzed using generalized estimating equation (GEE) models with an exchangeable correlation structure. Depending on the variable distribution, we will either use log-binomial or Poisson models. The GEE approaches allow us to examine differences in subgroups by first including interaction terms into the models. This will enable us to explore if the intervention differentially impacts subgroups of learners and care teams defined by a variety of variables of interest (e.g., age, sex, location, etc.). Similar longitudinal data analysis approaches will allow us to examine differences in outcomes between cohorts at FHCSD and UW. In order to investigate the time to uptake of specialist recommendations between cohorts, a Cox proportional-hazards model will be applied. In addition, Kaplan–Meier curves and log-rank tests will be performed.

Data from the semi-structured qualitative interviews will be transcribed verbatim, transcripts will be uploaded into N-Vivo (QSR International software) for qualitative analysis. We will use a three-phased thematic analysis technique to code the responses using deductive and inductive codes. Authentication of key themes will occur by discussion and consensus with the research team.

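### The subgroup GEE is fitted to intervention-arm clinicians only, so it cannot show whether the intervention works differently across subgroups

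*Protocol article*

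**What the plan says.** Under Statistical analysis, the protocol article states: "Changes over time among clinicians in the intervention condition will be analyzed using generalized estimating equation (GEE) models with an exchangeable correlation structure". The Intervention(s) section gives the size of that set: "Of the 20 participating clinicians, 10 will be randomized to weekly teleECHO sessions". On the model family, it says: "Depending on the variable distribution, we will either use log-binomial or Poisson models". On subgroups it says: "The GEE approaches allow us to examine differences in subgroups by first including interaction terms into the models", and gives the purpose: "This will enable us to explore if the intervention differentially impacts subgroups of learners and care teams". Age, sex and location are given as examples of subgroup variables.

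The same section describes a separate two-arm linear mixed model for patient and clinician outcomes. Its listed fixed effects are arm, assessment, their interaction, the baseline value and unbalanced covariates. No subgroup term is listed. A two-sided 5% level is set for all tests.

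The Quarterly survey section says that clinicians in both arms complete the surveys. The Researchers section lists total caseload, caseload of the target conditions and specialist referrals for all trial clinicians. Cases presented to the panel and specialist recommendations applied are listed for the 10 intervention clinicians only.

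**The concern.** The purpose given for the interaction terms is causal: for whom does the intervention do more? The population named for the model has no comparator. The article itself supplies rival reasons why subgroups might change at different rates:

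- Both arms receive the monthly webinars and quarterly short courses, and the courses are built from the key findings of the teleECHO sessions.
- Clinicians are followed for 30 months in a field that the Background calls evolving.
- The Discussion expects the common clinical issues to change over time.

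If younger clinicians, say, pick up new guidance faster whatever their arm, a one-arm subgroup-by-time term would record that as teleECHO working better in younger clinicians. The result would be mislabelled, although the data for a better answer are already being collected. The Background criticises earlier teleECHO evaluations for lacking randomization and well-characterised comparison groups; this analysis gives up the comparison group that the trial has.

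Two smaller matters follow from the same sentences: how tests behave with only 10 clusters, and whether the two named model families suit 5-point survey items.

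**Working it through.** **1. What the one-arm term estimates.** On the model (log) scale, let subgroup s change at rate A_s without teleECHO (secular learning plus the shared webinars and courses), and let teleECHO add B_s.

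- Intervention arm, subgroup-by-time: (A_1 − A_0) + (B_1 − B_0).
- Control arm, subgroup-by-time: (A_1 − A_0), equal in expectation because clinicians are randomized.
- Difference, i.e. arm-by-time-by-subgroup: (B_1 − B_0).

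Differential impact is B_1 − B_0. The one-arm term equals it only if A_1 = A_0. A trend that is the same in both subgroups on the log scale cancels; a trend that differs by subgroup does not. No choice of variance or correlation structure changes this.

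**2. Precision of the two-arm version.** At an even split, 20 clinicians / (2 arms × 2 subgroups) = 5 per cell. With v the variance of one clinician's change, the one-arm contrast has variance v(1/5 + 1/5) = 0.4v and the two-arm contrast v(4/5) = 0.8v. The standard error rises by √2, about 1.41 times.

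**3. Test size with 10 clusters (conditional).** The plan gives no figure for this GEE beyond the nominal 5% level, so there is none to reproduce. It names no variance estimator or reference distribution. The figures below assume the uncorrected sandwich with critical value 1.96.

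Analytic approximation, with K clusters and df degrees of freedom: size = 2 × P(t_df > 1.96 × √(df/K)).

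- Time trend, K = 10, df = 9: 1.96 × √0.9 = 1.859, size 9.6%.
- Two subgroups of 5, K = 10, df = 8: 1.96 × √0.8 = 1.753, size 11.8%.

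Simulation under no effect: exchangeable GEE, 10 clinicians, 1,200 to 1,500 runs per setting. Assumed, because the article gives no values: mean count 10 and random-intercept SD 0.4 for Poisson; event rate 40% and random-intercept SD 0.7 on the logit scale for binary.

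| Setting, uncorrected sandwich with z | Time trend | Subgroup-by-time |
|---|---|---|
| Poisson, baseline plus the 7 planned visits, 5/5 split | 11.2% | 11.8% |
| Same, 3/7 split | 8.9% | 17.8% |
| Poisson, 8 equally spaced occasions, 5/5 | 9.6% | 14.6% |
| Same, with random slopes (SD 0.3) | 12.5% | 13.0% |
| Poisson, 2 occasions, 5/5 | 10.9% | 12.3% |
| Binary, 8 occasions, 5/5 (logit standing in for log-binomial) | 8.3% | 10.4% |

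With a bias-reduced variance and a t reference (9 df for time, 8 df for subgroup), the first two rows become 4.6% and 3.3%, and 4.4% and 6.8%. Simulation error is about 1 point: √(0.12 × 0.88 / 1,200) = 0.009.

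**4. Model family.** The Quarterly survey section says of knowledge and self-efficacy: "This 5-point response format will be held constant across survey knowledge and self-efficacy statements", with an index to be formed for more exploratory use. Neither log-binomial nor Poisson describes a 5-point item or such an index, and the article states no dichotomisation. Referral counts and binary or proportion measures do suit those families.

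**The case against.** The strongest reply is that this analysis is exploratory and supplements a two-arm comparison. The effectiveness conclusion rests on the arm-by-assessment contrast in the mixed model, and some clinician measures have no control counterpart, so for them a one-arm model is the only option. All of that stands; it limits the weight of the point and shapes the fix. It does not rescue the stated purpose for outcomes measured in both arms, because the mixed model lists no subgroup term.

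The word learners may also reach beyond the 10 clinicians, since the Learners section covers webinar and course participants outside the trial. But no other population is named for the GEE, and outside learners have no randomized comparator either.

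Three stronger readings are tempting and are not supported:

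- **That the GEE tests will run at 11-12%.** The article is silent on the variance estimator, and a small-sample correction is a detail it may leave to the full protocol or an analysis plan. The inflation is conditional, and it is a range.
- **That secular trends in general would pass as differential effects.** Only trends that differ by subgroup on the model scale do so.
- **That no suitable model exists for the survey scales.** A linear mixed model is planned for clinician outcomes between arms, and nothing assigns the 5-point items to Poisson. The mismatch arises only if they enter the within-arm GEE.

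**Conclusion.** The point holds for the subgroup claim. As written, the model population and the stated purpose do not match: a GEE in 10 intervention-arm clinicians can describe differing change by subgroup but cannot identify differing intervention impact. This follows from the design and needs no numerical assumption. The size of any resulting bias is A_1 − A_0, which the article gives no means to estimate.

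The consequence is a mislabelled exploratory finding about who benefits, not a threat to the primary patient outcome. It should be corrected, but it is not critical.

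The test-size point is secondary. If the uncorrected sandwich with a z reference were used, nominal 5% tests would run at about 8-18%, depending on outcome type, contrast and subgroup split (time trends roughly 8-12.5%, subgroup terms roughly 10-18%), against about 3-7% with correction. These ranges rest on assumed means and variances. The model-family point applies only if 5-point items or their index are analysed in this GEE.

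**What to change.** 1. **Outcomes collected in both arms** (quarterly surveys, caseload, referrals): fit the exploratory subgroup question in all 20 clinicians and report the arm-by-time-by-subgroup contrast with its interval. State that precision is low, at about 5 clinicians per cell for an even split.
2. **Outcomes that exist only in the intervention arm** (cases presented, recommendations applied): keep the one-arm model, and describe results as within-arm change by subgroup rather than differential impact.
3. **Variance**: state a bias-corrected sandwich (Mancl-DeRouen or Kauermann-Carroll) with a t reference on clusters minus parameters. Keep it for the 20-clinician models, where the same analytic formula for a two-group contrast still gives 7.9% uncorrected (K = 20, df = 18).
4. **Model family**: if 5-point items or the index enter the within-arm GEE, use a Gaussian or ordinal model for them. Keep log-binomial or Poisson for binary items and counts.

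The cost is a few sentences and a few lines of code. No new data are needed. Intervals will be wider: the two-arm subgroup contrast has a standard error about 1.41 times that of the one-arm term, and the small-sample correction widens intervals further.

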#### Weekly teleECHO sessions

During the last 10 min of each weekly teleECHO session, intervention clinicians will be asked to follow a link to a web-based survey, loaded in REDCap. This semi-structured survey has three objectives: (1) to gather data required for the participants to receive CME credit, (2) to gather data useful for assessing feasibility and utility of the teleECHO model, and (3) to gather data on format and content of the sessions to guide program improvement. CME credit is offered by Project ECHO, University of New Mexico (UNM) to intervention providers who attend each session. To be eligible for this credit, clinicians are required to complete 20 post-session questions that are universal for every teleECHO session, which explore session relevance, achievement of course objectives, pace and delivery of the session content, and what participants liked most or least about the session. Additionally, we ask clinicians to rate their knowledge of the session content before and after the session, to explore knowledge gains, and if and how they intend to apply course content to their care of patients with PCC, ME/CFS, and other PIFI patients.

Making time within the session for this survey and making these questions mandatory for CME credit is expected to result in better survey compliance. The survey will last approximately 10 min and we will leave the survey available for a short time after the session to help clinicians complete the survey who might have been interrupted for any reason. If survey compliance is under 50%, a reminder email will be sent in a timely manner prior to the survey closing. Intervention clinicians’ survey responses will not be strictly confidential, as the questions are required to be documented by individuals for CME credit. With every survey, we will encourage clinicians to be candid in their responses, so that we can improve the ability of the teleECHO session curriculum to meet their needs. While this lack of anonymity presents a risk for bias, we will have the opportunity to assess similar constructs of utility and satisfaction in the quarterly surveys of participating clinicians, which will be strictly confidential and de-identified. This will help us to assess any bias and take further measures to reduce bias if needed.

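### The GEE analysis of change in the 10 teleECHO clinicians allows only log-binomial or Poisson models, and neither suits the 5-point knowledge and self-efficacy ratings (minor)

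*Protocol article*

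**What the plan says.** All references are to the protocol article.

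- **Statistical analysis, within-arm change:** "Changes over time among clinicians in the intervention condition will be analyzed using generalized estimating equation (GEE) models with an exchangeable correlation structure". The outcome model is then fixed: "Depending on the variable distribution, we will either use log-binomial or Poisson models". No outcomes are listed and none are excluded; the only selection rule is the distribution of the variable.
- **Intervention(s):** "Of the 20 participating clinicians, 10 will be randomized to weekly teleECHO sessions", so this analysis has 10 independent units.
- **Quarterly survey:** "This 5-point response format will be held constant across survey knowledge and self-efficacy statements, to allow for an index to be created". The index is meant for exploratory use. The same section gives change in knowledge, self-efficacy and clinical behaviour as what the clinician data are meant to document.
- **Measures, Weekly teleECHO sessions:** "we ask clinicians to rate their knowledge of the session content before and after the session". This survey goes only to intervention clinicians. Its response scale is not stated.
- **Statistical analysis, between-arm comparison:** "Analyses of differences in outcomes at both the patient- and clinician-level will include a linear mixed model", which compares change between the randomised arms and reports mean differences.
- **Researchers:** two measures kept only for the intervention clinicians are the proportion of cases taken to the specialist panel and the number of specialist recommendations applied.
- **Statistical analysis, cohorts:** "Similar longitudinal data analysis approaches will allow us to examine differences in outcomes between cohorts at FHCSD and UW".

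**The concern.** A log-binomial model is for yes/no data and a Poisson model is for counts. A 5-point agreement rating, or an index averaged from several, is neither. The sentence names two families and provides no third, so an analyst who follows it with the ratings has two routes.

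The first is to cut each item, for example agree or strongly agree against the rest. This discards all movement on either side of the cut. The second is to treat a bounded rating as a count. This keeps the scale but reports a ratio of means whose size depends on whether the lowest category is coded 0 or 1.

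The linear mixed model does not fill the gap. It addresses differences between arms, and the before/after session ratings have no control-arm counterpart. For those ratings, the GEE sentence is the only quantitative change model that the article offers.

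At stake is whether a real gain in knowledge or confidence among 10 clinicians is seen and reported on an interpretable scale.

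**Working it through.** **The plan's own figure.** The article states no power, effect size, SD or correlation for any clinician outcome, so there is no figure to reproduce for this analysis. Its 80.0% to 87% is for the patient primary outcome. It reproduces: design effect 1 + (30 − 1) × 0.1 = 3.9; effective n = 300/3.9 = 76.9 per arm; power 79.7% at d = 0.45 and 87.3% at d = 0.50. It has no bearing on this point.

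**Inputs.** From the article: 10 clinicians, a 5-point scale, two-sided 5% tests. Assumed: a latent normal rating cut into five categories, measured at baseline and at one later visit; a latent shift; and a within-clinician correlation.

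**Route 1, cut to yes/no.** The same paired t-test (9 df) is applied to the 1–5 score and to the indicator of a score of 4 or more. With 35% agreeing at baseline and correlation 0.5:

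| Latent shift (SD) | 5-point score | Agree / not agree | Loss (points) |
|---|---|---|---|
| 0.8 | 53% | 34% | 19 |
| 1.0 | 72% | 49% | 23 |
| 1.2 | 85% | 63% | 22 |

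Over 24 settings (shift 0.6, 0.8, 1.0 or 1.2 SD; correlation 0.3 or 0.5; 20%, 35% or 50% agreeing at baseline), the loss is about 6 to 28 points. A wider grid (shift 0.3 to 1.0 SD; correlation 0.3 to 0.7; other baseline distributions) gives 1.4 to 43.5 points.

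This risk-difference test is the kinder version of the cut. A log-link Wald test, which is closer to a log-binomial fit, does worse. With category limits at ±0.5 and ±1.5 SD, correlation 0.5 and shift 0.8 SD, power goes from 52.8% on the 5-point score to 1.0% (t, 9 df).

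**Boundary.** If 50% agree at baseline, the probability of agreeing after a shift s is Φ(s). The chance that all 10 agree at follow-up is Φ(s)^10:

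- s = 1.0: 0.841^10 = 0.18
- s = 1.2: 0.885^10 = 0.29, against up to 30% in simulation

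In those trials the fitted proportion is 1, which is the edge of what a log-binomial model can fit.

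**Route 2, Poisson with robust variance.** With the same category limits (±0.5 and ±1.5 SD) and correlation 0.5:

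| Latent shift (SD) | 5-point score | Poisson | Agree / not agree |
|---|---|---|---|
| 0.5 | 24.2% | 23.4% | 14.8% |
| 0.8 | 52.8% | 50.9% | 34.2% |
| 1.0 | 71.0% | 68.8% | 49.4% |

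Over the wider grid, the Poisson loss runs from −0.8 to +3.0 points. Over the 24 settings it is about 1 to 4 points. The cost is in interpretation. A group mean that moves from the middle category to the next gives 4/3 = 1.33 if coded 1–5 and 3/2 = 1.50 if coded 0–4.

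**Closer to the planned model.** This run used an exchangeable GEE over eight waves (baseline plus seven follow-ups), correlation 0.5 and 300 replicates. The yes/no fit used a log link with Poisson working variance. Power for Gaussian / Poisson / yes-no was 32 / 29 / 11% at shift 0.5 SD and 66 / 65 / 32% at 0.8 SD. The simulation error is up to about 3 points (√(0.66 × 0.34/300) = 0.027). The pattern is the same: the cut costs power and Poisson hardly does.

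**The case against.** The strongest reply is that the GEE sentence names no outcomes. Two measures kept only for the intervention arm, a proportion and a count, fit its two families well. The 5-point survey goes to both arms, and its comparison with control falls under the linear mixed model, which keeps the full scale. Nowhere does the article say that a rating will be dichotomised. It also condenses a fuller protocol, and matching outcomes to model families is detail that an analysis plan may hold.

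Much of this stands, and it limits the point. What remains is that the article states a rule, and the rule is closed: it covers change over time in these clinicians without restriction and names no family for a rating. The before/after session ratings have no other quantitative model.

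Four stronger readings are tempting but not supported:

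- **The ratings must be cut.** Poisson is also allowed, and it keeps the scale.
- **The plan as a whole costs 6 to 28 points of power.** That range belongs to the yes/no route alone and rests on assumptions that the article does not supply.
- **The linear mixed model and the GEE contradict each other.** One compares randomised arms and the other describes change within one arm, so they are different analyses.
- **PROMIS T-scores will be split in the FHCSD–UW comparison.** The article says only that the approaches will be similar. Applying the trial's 300 per arm and ICC of 0.1 to that non-randomised comparison would not describe it.

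**Conclusion.** The point holds as a minor one. The stated choice of families has no suitable member for the knowledge and self-efficacy ratings, their index or the session ratings.

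If ratings are cut to yes/no, the loss with 10 clinicians is material: roughly 6 to 28 points under shifts of 0.6 to 1.2 SD and correlations of 0.3 to 0.5, and wider under other assumptions. The model can also reach its boundary when everyone agrees. If ratings are modelled as Poisson with robust variance, power is nearly kept (a loss of about 0 to 4 points), but the effect measure depends on the coding.

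The sizes are illustrative, because the article gives no effect size or correlation for clinicians. The direction does not depend on the exact values: the cut lost power in every setting tried. The analysis is non-randomised, within one arm and unpowered, so neither the randomised comparison nor the patient primary outcome is touched.

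**What to change.** In the Statistical analysis section, replace the sentence that offers only two families with a rule by outcome type:

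- **Ratings and their index:** identity-link (Gaussian) GEE or a linear mixed model, with an ordinal model as an option for single items. Report mean change with a 95% confidence interval.
- **Naturally binary outcomes and proportions,** such as cases taken to the specialist panel: log-binomial.
- **Counts,** such as recommendations applied: Poisson.

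Also state which clinician outcomes the GEE covers, and that the same rule applies to the FHCSD–UW comparison, so that continuous scores there are analysed as continuous.

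The cost is a few lines of wording and no new data. The only downside is that results appear in rating-scale units; the percentage agreeing can still be shown descriptively.
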